## Abstract

**Background:**

S-adenosyl methionine (SAMe) is a pivotal metabolite in multiple pathways required for neuronal homeostasis, several of which are compromised in Alzheimer’s disease (AD). Correction of the SAMe deficiency that is characteristic of the AD brain may attenuate or prevent pathological processes driving AD-associated neurodegeneration including aberrant tau hyperphosphorylation and DNA hypomethylation.

**Objectives:**

The primary aim is to test the hypothesis that daily treatment with 400 mg oral SAMe for 180 days will lead to a greater reduction from baseline in plasma levels of p-tau181 compared to placebo in patients with mild cognitive impairment or dementia due to AD.

**Design, Setting, Participants:**

This is a phase II, randomized, multi-center, double-blind, placebo-controlled trial among 60 participants with mild cognitive impairment or dementia due to AD. Participants will be randomized in a 1:1 ratio to receive either SAMe or matching placebo, to be taken as an adjunct to their AD standard of care.

**Measurements and Results:**

The primary outcome is change in plasma p-tau181 concentration between baseline and following 180 days of treatment, which will be compared between the active and placebo group. Secondary outcomes are the safety of SAMe administration (incidence of serious adverse events), change from baseline in cognitive performance (as measured by the Repeatable Battery for the Assessment of Neuropsychological Status), and epigenetic changes in DNA methylation.

**Conclusion:**

Demonstration of effective and safe lowering of plasma p-tau181 with SAMe in this phase II trial would pave the way for an exciting field of translational research and a larger phase III trial.

**Electronic Supplementary Material:**

Supplementary material is available in the online version of this article at 10.14283/jpad.2023.55.

## Introduction

Plaques containing amyloid-β (Aβ), and neurofibrillary tangles consisting of hyperphosphorylated tau are the core pathological hallmarks of Alzheimer’s disease (AD). Overproduction and reduced clearance of Aβ are the key drivers of the disease, and Aβ toxicity and neurodegeneration are mediated through tau (1). Both Aβ and tau are also well-validated biomarkers of AD (2). As such, reduction of Aβ and/or tau levels is a prime target of therapeutic trials currently underway around the world. Aberrations in multiple molecular pathways contribute to the development and progression of AD pathology including tau hyperphosphorylation, DNA hypomethylation, and maladaptive neuroinflammation (3).

Despite advances in the understanding of the underlying mechanisms of AD, no effective disease modifying therapy exists. Results from clinical trials targeting single aspects of AD pathology, such anti-Aβ therapy, have been mixed. An attractive strategy would be to identify and target an ‘upstream’ aberration at the convergence of several pathological processes leading to the clinical manifestations of AD. This strategy is challenging given the diverse genetic, lifestyle, nutritional, and environmental risk factors that contribute to AD pathogenesis. None alone can account for the total prevalence of the disease; it is likely that disease manifestation occurs when multiple risk factors coalesce. For example, a genetic predisposition may become unmasked in the presence of age-related malnutrition, or changes in neuronal homeostasis.

S-adenosyl methionine (SAMe), the active form of the amino acid methionine, is the major metabolite in multiple metabolic pathways on which neuronal homeostasis depends. As a methyl donor, SAMe influences gene expression (via DNA methylation) and results in the synthesis of diverse products including neurotransmitters and phosphatases (4). SAMe is central to transsulfuration (which produces glutathione, the brain’s major antioxidant (5)), and the synthesis of neuroregulatory polyamines (which have anti-inflammatory properties (6) and are involved in controlling cell differentiation and proliferation (7)).

Maintenance of these processes, and thus normal neuronal function, depends on an adequate source of SAMe. Significantly reduced SAMe concentrations have been identified in both the cerebrospinal fluid (8) and postmortem brain tissue (9) of patients with AD. The cause of SAMe depletion in the AD brain is likely multifactorial (see Fig. 1). Contributing factors may include B12 or folate deficiency (since methionine generation requires these nutrients), or excessive SAMe utilization in polyamine synthesis as part of a maladaptive chronic inflammatory response to tau pathology (10, 11). Elevated homocysteine, a sequela of B12 and folate deficiency, can also inhibit SAMe’s methylation function via negative feedback on methionine cycle enzymes (see Fig. 2 A and B) (12).

**Figure 1 Fig1:**
[figure not shown]
Causes and consequences of S-adenosyl methionine (SAMe) deficiency in AD

Several factors contribute to the SAMe deficiency characteristic of the AD brain including malnutrition, hyperhomocysteinaemia, excessive SAMe consumption in polyamine synthesis in the setting of chronic neuroinflammation, and other as-yet unknown mechanisms. SAMe deficiency accounts for multiple key pathological processes characteristic of AD. PP2A, the brain’s major phosphatase, is dysfunctional without methylation, allowing tau hyperphosphorylation to proceed unchecked. Loss of methylation of AD-associated genes (or their promotors) results in their expression. Brain acetylcholine levels fall owing to deficient SAMe-mediated methylation of N-methyl nicotinamide, which usually prevents the physiological net efflux of acetylcholine from the brain. Loss of SAMe-mediated transsulfuration depletes brain glutathione levels, impairing cerebral antioxidant activity and perpetuating neuroinflammation. AD: Alzheimer’s disease, P: phosphate, PP2A: protein phosphatase 2A

**Figure 2 Fig2:**
[figure not shown]
A) The methionine cycle. Methionine is activated by adenosine triphosphate (ATP) to form S-adenosyl methionine (SAMe). In the process of methylation, SAMe donates a methyl group to a substrate in a reaction catalyzed by a methyltransferase. The remaining product, S-adenosyl homocysteine (SAH) is converted to homocysteine. From here, homocysteine has two possible fates: transsulfuration to glutathione (a B6-dependent reaction) or remethylation to methionine (a vitamin B12-dependent reaction, using methyl tetrahydrofolate as a substrate). The latter produces much of the methionine required to generate new SAMe. B) Aberrations in the methionine cycle leading to quantitative and functional SAMe deficiency

1. B12 or folate deficiency mean that homocysteine cannot be remethylated to methionine. These deficiencies may be quantitative (e.g. due to malnutrition) or functional (i.e. due to cerebral oxidative stress (25)). 2. SAMe levels fall due to lack of methionine (activation of dietary methionine is inadequate to meet the body’s SAMe needs; the body relies on de novo methionine synthesis generated via remethylation of homocysteine to sustain SAMe concentrations (24)). 3. Unable to be remethylated, homocysteine accumulates. 4. To achieve equilibrium, some excess homocysteine is converted back to SAH. 5. SAH is a potent inhibitor of methyltransferases with a much greater affinity for these enzymes than SAMe. As such, the low levels of SAMe remaining are unable to perform vital methylation reactions (i.e. functional SAMe deficiency).

Regardless of cause, SAMe deficiency exacerbates several key processes that underpin AD pathophysiology. SAMe deficiency increases the expression of genes involved in the onset and progression of AD, leading to increased Aβ production (13–16); compromises acetylcholine production and retention in the brain (17); impairs phosphatase function, resulting in accumulation of hyperphosphorylated tau (18); and hinders glutathione-driven quenching of reactive oxygen species (19) promoting a neuroinflammatory state.

There is preclinical evidence suggesting that SAMe supplementation improves cognition in multiple animal models of neurodegenerative conditions including the 3xTg mouse model of AD (17, 20, 21). In humans with AD, SAMe administration as a component of a nutraceutical supplement resulted in improvements in both cognitive function and dementia symptom severity, with excellent tolerability (22, 23).

Widespread predominantly non-prescription use of SAMe currently occurs mainly for depression, osteoarthritis and liver disease, although the quality of evidence supporting these uses is limited (24). Given SAMe’s critical role in multiple pathological processes central to AD development, a unique opportunity exists to examine the efficacy and safety of this cheap, readily available, oral medication in a clinical trial of patients with AD.

## Methods

This is a phase II, randomized, multi-center, double-blind, placebo-controlled trial to assess whether treatment with 400 mg of oral SAMe for 180 days will reduce plasma p-tau181 levels in patients with mild cognitive impairment or dementia due to AD. Key trial activities are summarized in Fig. 3. After baseline data collection, participants will be randomized in a 1:1 ratio to receive either 400 mg SAMe or matched oral placebo to be taken as an adjunct to their AD standard of care. Participants will be assessed for safety at 30, 90 and 180 days from treatment commencement, and at 14 days following treatment cessation. Efficacy will be determined by comparing data collected after 180 days of treatment with baseline assessments.

**Figure 3 Fig3:**
[figure not shown]
Summary of SAMe Study design. Participants will complete 6 study visits

Each blue column summarizes the visit number, its timing and key purpose, and the study activities performed during the interaction. Visit 1 comprises obtaining informed consent, screening for eligibility, enrollment if suitable, and baseline data collection. Randomization and study drug dispensation occurs at visit 2, which constitutes ‘day 0’. Visits 3 and 4 involve safety assessments. Endpoint data collection occurs at visit 5. Visit 6 entails a follow-up telephone call to the participant for a final adverse event report. Visits will occur within an allowed range of days around the desired timepoint (indicated by ±). The endpoint data collection visit (visit 5) does not have an upper allowable bound: endpoint data is to be collected within the final 10 days of the participant’s 180 days taking the study drug. *:vital signs, body weight, physical examination; @: full blood examination, general biochemistry, liver function tests, coagulation studies, vitamin B12, folate, homocysteine; ^: Repeatable Battery for the Assessment of Neuropsychological Status, Standardized Mini-Mental State Examination, Cognitive Dementia Rating, California Verbal Learning Test 3rd Edition, Montreal Cognitive Assessment, Digit Symbol Substitution Test, Geriatric Depression Scale. ApoE: apolipoprotein E; CDR: Cognitive Dementia Rating; p-tau181: phosphorylated tau181; SAMe: S-adenosyl methionine.

The trial has been prospectively registered on australianclinicaltrials.gov.au (ACTRN12620000506998) and will be conducted within the estimand framework for the design and analysis of clinical trials. Briefly, the objective of the estimand framework is to align the clinical trial objectives with the study design, endpoints and analysis, in order to improve study planning and the interpretation of study results (26). The trial design and estimands include prespecified strategies for the conduct of the trial during the COVID-19 pandemic (27–29). The protocol is reported according to SPIRIT guidelines, modified through inclusion of estimand framework (30).

This study will be conducted in accordance with the Declaration of Helsinki and Council for International Organizations of Medical Sciences International Ethical Guidelines. The protocol has been approved by the local Human Research Ethics Committee.

### Aims and hypotheses

#### Primary aim

The primary aim is to test the hypothesis that treatment with 400 mg per day of oral SAMe for 180 days will lead to a greater reduction from baseline plasma levels of p-tau181 compared to placebo in patients with mild cognitive impairment or dementia due to AD.

#### Secondary aims

Secondary aims are to determine if, compared to placebo, treatment with 400 mg oral SAMe for 180 days will 1) maintain or improve performance as measured by the Repeatable Battery for the Assessment of Neuropsychological Status (RBANS), 2) result in epigenetic changes in DNA methylation, and 3) be safe.

### Exploratory aims

Exploratory aims are to evaluate the change from baseline that treatment with 400 mg oral SAMe for 180 days has, compared to placebo, on 1) blood total tau, amyloid-β, and neurofilament light levels, and 2) cognitive status as assessed by the Standardized MiniMental State Examination, Cognitive Dementia Rating, California Verbal Learning Test 3rd Edition, Montreal Cognitive Assessment, and Digit Symbol Substitution Test.

### Participants and setting

Community-dwelling adults aged 60 years and older with mild cognitive impairment or dementia due to AD who meet all other inclusion criteria will be eligible for recruitment, provided no exclusion criteria are met.

### Inclusion criteria

- Male and female individuals of at least 60 years of age at the time of the screening visit- Diagnosis of mild cognitive impairment (31) or dementia (32) due to AD according to NIA-AA 2011 criteria- Standardized mini-mental state examination score of at least 18 at the time of the screening visit- Living in a community setting without continuous nursing care- Can identify a reliable study partner with whom they have at least 3 weekly interactions to oversee study drug administration and participate in all clinic visits and some study procedures (including Cognitive Dementia Rating).- If taking medications indicated for control of AD symptoms, on stable doses for at least 8 weeks prior to screening

### Exclusion criteria

- Any history of bipolar affective disorder- A medical condition, other than AD, that may contribute to the individual’s cognitive impairment- Stroke or transient ischemic attack in the past 12 months- Clinically significant unstable psychiatric condition in the past 6 months- Inability to swallow oral medications- Other medical conditions which the investigator deems would limit the individual’s life expectancy to less than 6 months- Concurrent use of anti-depressant medication- Participation in another interventional clinical trial, or intake of another investigations drug within 4 weeks or 5 half-lives (whichever is longer)

### Study Estimands

#### Primary estimand

Population: all included participants.Individual level outcome measure: percentage change in plasma p-tau181 concentration (comparing baseline to 180 days). P-tau181 levels will be measured using the single-molecule array (Simoa) technique according to the manufacturer’s instructions (Quanterix Corp., US).Population level outcome measure: difference in means between intervention and control groups adjusted for baseline p-tau181 level.

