### Sample size

Allowing for potential participant attrition, the total sample size for the study is 60 (30 per arm). Sample size calculations assumed a two-tailed alpha of 0.05 and a similar baseline standard deviation between the two arms. A total sample size of 52 participants (26 per arm) would yield 80% power to observe a large treatment effect (Cohen’s d 0.8). This sample size estimation is conservative in the sense that including the baseline p-tau181 concentration in the final ANCOVA model would increase the power.

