### Statistical analysis

All outcomes and analyses are prospectively categorized as primary, secondary or exploratory. Differences in all endpoints between the 2 arms of the study will be tested independently at the two-tailed 0.05 level of significance. All estimates of treatment effects will be presented with 95% confidence intervals. The primary endpoint will be tested using an ANCOVA model with treatment arm as an independent variable and baseline blood p-tau181 concentration as a covariate. Between group differences in secondary and exploratory outcomes will be assessed using regression models as appropriate to the response outcome distribution using baseline values of the respective outcomes as adjustment covariates. The detailed analysis will be prespecified in a formal statistical analysis plan which will be finalised prior to the study database lock.

No formal adjustments will be undertaken to constrain the overall type I error associated with the secondary and exploratory analyses. Their purpose is to supplement evidence from the primary analysis to characterize the treatment effect more fully. Results from the secondary analyses will be interpreted in this context.

Given that establishing biological efficacy is the primary objective of the trial, according to the pre-specified estimand, all participants who achieve at least 80% study medication compliance and provide a 180-day blood sample will be included in the primary efficacy analysis. All participants who provide both baseline and end of treatment blood samples will be included in a secondary dose-response analysis to account for potential early study withdrawals or poor compliance.

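### The primary endpoint is not named on one scale throughout, and the scale the estimand fixes, percentage change adjusted for raw baseline, was never more powerful than log-scale ANCOVA in any setting tried

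*Protocol article*

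**What the plan says.** All references are to the protocol article.

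- **Abstract, Measurements and Results:** "The primary outcome is change in plasma p-tau181 concentration between baseline and following 180 days of treatment". No scale is given.
- **Primary aim:** SAMe "will lead to a greater reduction from baseline plasma levels of p-tau181 compared to placebo". Again no scale.
- **Primary estimand:** the individual-level outcome is "percentage change in plasma p-tau181 concentration (comparing baseline to 180 days", and the population-level summary is the "difference in means between intervention and control groups adjusted for baseline p-tau181 level".
- **Statistical analysis:** "The primary endpoint will be tested using an ANCOVA model with treatment arm as an independent variable", with "baseline blood p-tau181 concentration as a covariate". The response is called only the primary endpoint, but the same section ties the primary efficacy analysis to the pre-specified estimand. No transformation is mentioned, and detail is deferred to an SAP to be finalised before database lock.
- **Sample size:** 26 per arm for 80% power at Cohen's d 0.8, with no scale named for d.

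Read together, the operative primary analysis is ANCOVA on percentage change with the untransformed baseline as covariate.

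**The concern.** There are two linked issues.

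First, absolute change and percentage change are different variables. A reader who takes the abstract at face value and one who takes the estimand could test different quantities on the same data and reach different verdicts. The article says that the trial follows the estimand framework so that objectives, endpoints and analysis line up, so one variable should run through all of them.

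Second, percentage change is a ratio with the baseline in the denominator. For a positive concentration it tends to be right-skewed, and low baselines inflate both its level and its spread. A linear term in raw baseline does not fully remove this. With 52 evaluable participants and power only just above 80%, there is little room for an inefficient response variable when an equally readable alternative exists.

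**Working it through.** **1. The plan's own figure.** Inputs from the Sample size section: d = 0.8, two-sided alpha 0.05, 26 per arm. For a two-sample t test the noncentrality is d × √(n/2) = 0.8 × √13 = 2.88 on 50 degrees of freedom, which gives power 80.7%. With 25 per arm it is 79.1%. So 26 per arm (52) reproduces exactly. It rests on a scale-free d and does not depend on which endpoint is meant.

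**2. Why percentage change behaves as it does.** Let b be baseline and f the 180-day value, log-normal with equal log-SDs and log-scale correlation r. With logs centred, log f = r log b + e, so f/b = b^(r−1) × exp(e). Both the mean and the SD of f/b vary as b^(r−1), which is curved in b. Halving the baseline multiplies both by 2^(1−r): 2^0.4 = 1.32 at r = 0.6, but only 2^0.1 = 1.07 at r = 0.9. This is why the loss fades at high correlation.

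**3. Assumed inputs.** The article gives no SD, skewness or baseline to follow-up correlation for p-tau181, so all of these are assumptions. Simulations used 26 per arm, with the effect set so that the correctly specified model has about 80% power. Log-SD = √ln(1 + CV²), so a coefficient of variation (CV) of 0.6 is a log-SD of √ln 1.36 = 0.55.

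**4. Power on log-normal data with a multiplicative effect** (4,000 trials per cell; Monte Carlo standard error of a power figure about √(0.8 × 0.2/4000) = 0.6 points):

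| CV | Correlation | Percentage change, baseline-adjusted | Log ANCOVA | Loss (points) |
|---|---|---|---|---|
| 0.4 | 0.60 | 75.2% | 78.7% | 3.5 |
| 0.4 | 0.75 | 77.8% | 80.0% | 2.2 |
| 0.4 | 0.90 | 79.3% | 80.1% | 0.8 |
| 0.6 | 0.60 | 71.8% | 79.2% | 7.4 |
| 0.6 | 0.75 | 76.9% | 80.8% | 3.9 |
| 0.6 | 0.90 | 77.9% | 79.4% | 1.5 |

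At log-SD 0.2 (CV about 0.2), with 20,000 trials per cell, the loss was 0.7 points at correlation 0.7 (79.3 v 80.0%) and 0.2 points at 0.9 (80.2 v 80.4%). The most skewed setting tried, log-SD 0.8 with correlation 0.5, gave 61.3 v 80.1%, a loss of 18.8 points. That is an extreme case, outside the CV and correlation range used for the conclusion.

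**5. Power on normal data with an additive effect** (20,000 trials per cell, correlation 0.5 to 0.85):

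| CV | Absolute change | Percentage change | Log ANCOVA |
|---|---|---|---|
| 0.15 | about 80% | 78 to 79% | 79% |
| 0.30 | about 80% | 69 to 73% | 73 to 75% |

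Percentage change is again no better than log. Absolute change is best here.

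**6. Absolute change as such.** With baseline as covariate, ANCOVA on f − b and ANCOVA on f gave the same treatment estimate and standard error (largest difference about 1e-15). Using absolute change therefore costs nothing in itself. It differs from the log analysis only through the raw scale.

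**7. Do the two wordings give different verdicts?** On log-normal data (6,000 trials per cell, correlation 0.6 to 0.9, d = 0.8 on the log residual), baseline-adjusted absolute and percentage change disagreed on significance in about 5% of trials at CV 0.2, 10% at CV 0.4 and 16 to 17% at CV 0.6.

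**8. Type I error.** Null rejection was 4.3 to 5.8% in the 4,000-trial runs and 4.4 to 5.3% in the 20,000-trial log-normal runs, for every form. Validity is not at issue.

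**The case against.** The strongest reply is that the abstract is shorthand: change can cover percentage change, the estimand is specific, and the Statistical analysis section points back to it. That stands. The abstract does not say absolute, so the mismatch is an ambiguity.

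A second reply is that transformations belong in the SAP, which is not shown. That would answer a complaint that the log scale is missing. It does not answer this point, because the article does fix a scale, percentage change with raw baseline, and that choice is open to comment.

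A third is that the efficiency loss is modest and rests on assumed distributions. This also stands: five of the six losses tabulated are under 4 points.

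Three stronger readings are tempting and not supported:

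- *Both change measures are always less efficient than log.* A reader might infer this from the log-normal runs alone, where the log model is the correct one. Under normal additive data absolute change beats log by up to 7 points, and the article gives no distribution to choose between the cases.
- *The sample size uses the wrong SD.* The text says only that the calculation "assumed a two-tailed alpha of 0.05 and a similar baseline standard deviation between the two arms", which reads as an equal-variance assumption. It does not say that d is scaled by the baseline SD, and 26 per arm reproduces.
- *The conservative claim is wrong.* The article says that "including the baseline p-tau181 concentration in the final ANCOVA model would increase the power", without an amount. On the log scale with equal SDs, baseline removes (1 − r)/2 of the variance of change: 5% at r = 0.9 and 20% at r = 0.6. The gain can be small, but the direction is right.

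**Conclusion.** The point holds in a limited form. The estimand fixes percentage change adjusted for raw baseline and the abstract does not match it. The difference matters, because the two scales disagree on significance in about 5 to 17% of trials under assumed log-normal data with CV 0.2 to 0.6 and correlation 0.6 to 0.9.

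Percentage change had no more power than log ANCOVA in any setting tried, log-normal or normal. Over the same log-normal range the loss is about 0 to 7 points, negligible at low CV or high correlation. Every power figure depends on assumed variability, correlation and shape, none of which the article gives. Type I error is near 5% for all forms, 52 evaluable participants is correct for d = 0.8, and nothing here shows absolute change to be generally inferior. This is a worthwhile, inexpensive improvement; the planned test remains valid.

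**What to change.** Define the primary endpoint once and use the same wording in the abstract, primary aim, primary estimand, sample size and statistical analysis. State in the sample size section the scale to which d = 0.8 refers.

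Preferably, make the response log(180-day p-tau181), analysed by ANCOVA with treatment, log(baseline p-tau181) and the age stratum used in randomisation (<70 v ≥70 years). Exponentiate the treatment coefficient to a ratio of geometric means and report 100 × (ratio − 1) as a percentage difference with its 95% confidence interval. The age term brings the model into line with the stratified randomisation; none of the figures above depends on it.

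If percentage change is kept, the minimum is to say so in the abstract and name it as the ANCOVA response.

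The cost is wording and one transformation, settled before database lock. Sample size, visits and assays are unaffected. The one real trade-off is that the target becomes a ratio of geometric means instead of a mean of individual percentage changes, so the estimand text must say so. The result still reads as a percentage.
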